### Statistical analysis

Baseline characteristics will be summarised by vaccination status for the whole cohort using mean, median or proportion where appropriate together with a measure of dispersion. We will evaluate the baseline characteristics of those tested and not tested using RT-PCR. Missing data will be reported for each variable. A 5% significance level will be used for hypothesis tests for the primary outcome. All p values will be two sided. All analyses will be undertaken in R (V.3.2.3; R Core Team (2015). R: A language and environment for statistical computing. R Foundation for Statistical Computing, Vienna, Austria. URL https://www.R-project.org).

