### Vaccine effectiveness

#### RT-PCR outcomes

For VE using information from linked virological RT-PCR swab data (a binary event) we will carry out a nested case test-negative control study.^19^ Influenza positivity will be compared with no influenza among patients who have ILI symptoms and tested for influenza. The primary analysis will be through a logistic generalised additive model where the effects of gender, age, socioeconomic status (SIMD^33^) and being in an at-risk morbidity group are adjusted for (a TND study). A spline function for time during each season will be included to model the background rate of influenza and correct for any potential bias associated with the proportions of test-negative and test-positive patients at different periods. VE will be measured by comparing the results from swabs taken after vaccination among those vaccinated to swabs taken among those unvaccinated at the time the swab is collected. Vaccination will be used to define exposure status if it was given at a time point between the 1 September and the end of the influenza season (figure 1). The adjusted estimate of VE=(1**−**OR)×100, where the OR is derived from the coefficient of vaccine status in the model. In our main analysis, we will assess only the first dose when two doses are given. We will carry out analysis stratified by influenza A (H1—including pandemic influenza and H3 subtype where recorded) and B.

We will carry out a number of sensitivity analyses for the primary end point:
*Non-sentinel* versus *sentinel*: We will explore the validity of using laboratory-confirmed influenza tests from non-sentinel primary care and secondary care sources versus sentinel primary care practices. Patient characteristics of individuals swabbed in non-sentinel primary care practices and secondary care will be described and any interaction between source of swab and outcome will be tested.*Negative controls*: As there should be no VE for influenza vaccine for these outcomes, we will explore the use of laboratory-confirmed infections (currently 10 respiratory viruses including rhinovirus and adenovirus) tested using multiplex RT-PCR at the same time as the influenza RT-PCR.*LAIV VE in younger/immunodeficient*: For younger vaccine-naïve or immunodeficient children receiving LAIV, we will account for any second dose in our model.

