### Sample size

We expect a final total sample size of up to 1.25 million from 220 practices. Using data from the PIPER 2014/2015 cohort, which has 263 000 individuals, 16% are aged 2–17, and 18% aged 65+.^48^ Vaccine uptake among children aged 3–12 years is 60% and vaccine uptake among those aged 65+ is 70%. Linked to this cohort from all virology tests in Scotland were 1745 RT-PCR tests overall; 331 RT-PCR tests among 2–17 years old; 366 RT-PCR tests among those aged 65+. This gives a multiplier ratio of around 5:1 from the PIPER cohort to the SIVE II cohort and this is used to estimate the numbers of RT-PCR tests expected each year. We expect 1800 RT-PCR tests per year among those aged 65+, 1650 laboratory tests per year among those aged 2–17. We expect 1745/12×5=630 patients with asthma swabbed per year as about 12% of the population is treated for asthma.

Using data generated from the SIVE project,^49^ we estimate a vaccination rate of 60% among children targeted for receipt of LAIV and a swab positivity rate of 20% among the unvaccinated. This should give 90% power to detect a VE of 31% based on 1650 swabs in one season. Pooling data over two seasons give an estimated 3300 swabs in children eligible for vaccination and a 90% power to detect a VE of 22%.

For 65+ year olds targeted for receipt of TIV where there is a vaccination rate of 70% and a swab positivity rate of 10% among the unvaccinated we anticipate an 80% power to detect a VE of 39% where we estimate that there will be 1800 swabs each year in the later years. During the peak influenza activity when swab positivity might increase to 20% there is a 90% power to detect a VE of 31%. About 1 in 12 of the population is treated for asthma^50^ and we anticipate 1260 swabs among patients with asthma in final two seasons. Assuming 40% are vaccinated and that the swab positivity is around 15% gives 80% power for a VE of 35%. For an influenza type/subtype which has 50% of the total cases, then the detectable VEs will be 40–50% with 90% power. For a type/subtype which has about 25% of the cases, then the detectable VEs will increase to over 60% with 90% power. These powers above do not take into account design effects for the clustering of patients within GP practices. Analyses of the historic PIPER cohorts^48^ has revealed design effect of <7% and this serves to increase the detectable VE by about two percentage points.

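### The unrestricted claim of 90% power at subtype VEs of 40–50% is not met for 65+ at 10% positivity in one season or for asthma, and the 65+ peak figure needs the whole year's swabs

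*Protocol article*

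**What the plan says.** The Sample size section gives detectable VEs for all influenza in three groups.

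- Children: "we estimate a vaccination rate of 60% among children targeted for receipt of LAIV and a swab positivity rate of 20% among the unvaccinated", with 1650 swabs in one season (VE 31%, 90% power) or 3300 over two (VE 22%, 90% power).
- 65+: 70% vaccinated, 10% positive among the unvaccinated, 1800 swabs a year (VE 39%, 80% power). It then adds "During the peak influenza activity when swab positivity might increase to 20% there is a 90% power to detect a VE of 31" per cent. No swab count is given for the peak.
- Asthma: 40% vaccinated, positivity around 15%, 1260 swabs over the final two seasons (VE 35%, 80% power).

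Two subtype statements follow the asthma figure directly. The first is "For an influenza type/subtype which has 50% of the total cases, then the detectable VEs will be 40–50% with 90% power". The second is "For a type/subtype which has about 25% of the cases, then the detectable VEs will increase to over 60% with 90% power". Neither names a group, a swab count, a positivity or a number of seasons.

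Under RT-PCR outcomes the protocol plans the matching analysis: "We will carry out analysis stratified by influenza A (H1—including pandemic influenza and H3 subtype where recorded) and B".

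**The concern.** A subtype with half the cases has half the positivity, so the VE that can be detected must rise. The 65+ base case and asthma reach only 80% power, at VE 39% and 35%, for all influenza together. The subtype sentence then moves to 90% power and half the cases, yet the quoted VE rises only to 40–50%. Because the sentence follows all three scenarios without restriction, a reader will apply it to all of them.

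The peak sentence raises a related doubt. It doubles the positivity for a period of high activity, but the only 65+ count in the section is for a whole year.

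Evaluating VE in people aged 65+ and people with asthma is part of the study's second objective. If subtype power there is overstated, a null subtype result could be read as absence of effect when the study had limited power to show one.

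**Working it through.** **Test.** Two proportions, two-sided 5% (Statistical analysis: "A 5% significance level will be used for hypothesis tests for the primary outcome"; "All p values will be two sided"). With N swabs and uptake v, n0 = N(1−v) are unvaccinated and n1 = Nv vaccinated. p0 is positivity in the unvaccinated, p1 = p0(1−VE), and p̄ is the pooled positivity. Then

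power = Φ{[(p0−p1) − 1.96·√(p̄(1−p̄)(1/n0+1/n1))] / √(p0(1−p0)/n0 + p1(1−p1)/n1)}.

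This treats VE as 1 − risk ratio (RR). The analysis model defines VE through an odds ratio ("the OR is derived from the coefficient of vaccine status in the model"), so results are also given with p1 taken from odds multiplied by (1−VE) (OR).

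**Step 1: the plan's overall figures, RR scale.**

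- Children, 1650 swabs, VE 31%: power 0.911 (plan 90%)
- Children, 3300 swabs, VE 22%: 0.901 (plan 90%)
- 65+, 1800 swabs at 10%, VE 39%: 0.811 (plan 80%)
- 65+, 1800 swabs at 20%, VE 31%: 0.900 (plan 90%)
- Asthma, 1260 swabs at 15%, VE 35%: 0.787 (plan 80%)

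All five agree within two points, so the method is evidently the plan's own.

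**Step 2: subtype with 50% of cases (p0 halved).**

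| Scenario | p0 | VE at 90% power, RR / OR | Power at VE 50%, RR / OR |
|---|---|---|---|
| Children, one season, 1650 | 0.10 | 43% / 46% | 97% / 95% |
| 65+, 1800 at 20% | 0.10 | 44% / 47% | 96% / 94% |
| 65+, one season, 1800 at 10% | 0.05 | 60% / 61% | 75% / 73% |
| Asthma, two seasons, 1260 | 0.075 | 56% / 58% | 80% / 76% |

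Worked line, 65+ at 10%, VE 50%, RR: n0 = 540, n1 = 1260, p0 = 0.05, p1 = 0.025, p̄ = 0.0325. The standard errors are 0.00912 (null) and 0.01036 (alternative). z = (0.025 − 1.96×0.00912)/0.01036 = 0.69, so power = 0.754.

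Worked line, asthma, VE 50%, RR: n0 = 756, n1 = 504, p0 = 0.075, p1 = 0.0375, p̄ = 0.06. The standard errors are 0.01366 and 0.01278. z = (0.0375 − 1.96×0.01366)/0.01278 = 0.84, so power = 0.799.

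At VE 40%, power on the RR scale is 55% (65+ at 10%) and 58% (asthma).

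Cross-check: for all influenza combined, 90% power already needs VE 44% in 65+ at 10% and 40% in asthma.

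**Step 3: other methods.** Continuity correction, unpooled variance, a Wald test on the log odds ratio, and removing other-type positives from the comparators were tried, as was reading asthma's 15% as overall positivity. The VE at 90% power ranged over 59–67% for 65+ at 10% and 51–62% for asthma. None fell within 40–50%. A design effect of 1.07 raises the RR values to about 62% and 58%.

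**Step 4: subtype with 25% of cases.** VE at 90% power, RR / OR: children 59% / 61%, 65+ at 20% 60% / 61%, 65+ at 10% 79% / 79%, asthma 76% / 76%.

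**Step 5: 65+ peak figure, 20% positivity, RR scale.**

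- All 1800 swabs: power at VE 31% is 0.900
- 75% of them (1350): 0.81; VE at 90% power 35%
- Half (900): 0.64; 42%
- 30% (540): 0.45; 53%

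The shares are assumptions, since the protocol gives none. If 10% is the average for the same season, a share f at 20% must satisfy 0.20f ≤ 0.10, so f could not exceed one half. With 900 swabs, the 50%-share subtype value at 20% positivity would be 59% (RR), not 44%.

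**The case against.** The strongest reply is that the subtype sentences are quoted at 90% power, and the section uses 90% only for children and for 65+ at 20% positivity. Those scenarios reproduce both statements for a single season. That stands. A reader might infer that the sentence is wrong throughout, and the documents do not support that. The fault is a missing restriction, and the figure fails where a reader would extend it.

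Pooling is a second reply. Annual and pooled analyses allows pooling across seasons when more precision is needed, particularly for subgroups. Two 65+ seasons at 10% (3600 swabs) give 45–46% for a 50% share and 60–61% for a 25% share. This stands in part: the Sample size section does not state pooling for 65+, and pooling depends on the heterogeneity test. The asthma figure already uses two seasons and still misses.

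Third, the asthma 15% is not said to apply to the unvaccinated. Read as overall positivity, it gives 51% (RR) or 53% (OR), only slightly outside the range.

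Fourth, a reader might call the 25%-share statement an error. It is not: 76–79% is above 60%. It is merely uninformative for these groups.

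Fifth, the use of 1800 swabs at peak is inferred from a numerical match. The sentence can be read as a season averaging 20% positivity, and then 1800 is legitimate. The wording points more naturally to part of a season, but this half remains conditional.

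Finally, the protocol does not say that the type/subtype stratification will be run within 65+ or asthma, and no analysis or decision rule depends on these figures. That limits the consequence to how results are read.

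**Conclusion.** The concern holds in limited form. The 40–50% statement is right for children in one season (43–46%) and for 65+ with 1800 swabs at 20% positivity (44–47%). It is not met for 65+ in one season at 10% (60–61%) or for asthma over two seasons (56–58%, or 51–53% if 15% is overall positivity). At the top of the stated range, VE 50%, power is 73–75% and 76–80% respectively, not 90%. This rests on the section's own uptake, positivity and swab counts, and on a method that reproduces its five overall figures.

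The peak figure is correct only if all 1800 yearly swabs are counted at 20% positivity. That it is overstated follows only if peak means part of a season, which the protocol does not settle.

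**What to change.** Replace the general subtype sentences with values by group, each with swab count, positivity, number of seasons and VE scale. For a 50% share at 90% power:

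- children, one season: about 43–46%
- 65+ at 10%, one season: 60–61%, or about 45% if two seasons are pooled and the text says so
- asthma, two seasons: 56–58%, stating whether 15% is positivity in the unvaccinated or overall

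For a 25% share, give about 59–61%, 79% and 76% for the same three groups, with 65+ in one season.

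For the 65+ peak figure, either recompute it with the swabs expected in the peak or state that it assumes a whole season at 20% positivity.

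The change is confined to the wording of the sample-size section; no analysis changes. The downside is that the stated figures become less favourable.

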#### Non-specific clinical outcomes

We will estimate VE for non-specific clinical outcomes: primary care consultations for ILI; all-cause emergency hospitalisation and death; and emergency hospitalisation and death due to influenza/pneumonia. Hospital admissions and consultations can have multiple events and each event will be counted.

For this proposal we have adopted methods we found in previous studies to be optimal for measuring VE and accounting for bias and confounding.^47^ Adjusted rate ratios of VE for prevention of hospitalisation/death/general practice consultation will be derived from time-dependent Cox models, taking into account the time at risk and the possibility of multiple events (not for death). Models will include a cluster term to account for intrapractice correlation. These models will adjust for gender, age, deprivation and clinical risk group and exposure to vaccination in each season included as a time-dependent covariate. Each season, individuals will begin in the unvaccinated group (and will accumulate time at risk) until 14 days after the receipt of the vaccine; then they will switch to the vaccinated group.

In all models used to estimate the VE, we will adjust for variables associated with the receipt of a vaccination and effect modifiers, such as vaccinations, consultations and hospitalisation in the previous influenza season, SIMD, urban/rural status, smoking status, Charlson score and pregnancy.

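### The stated powers are for an unadjusted comparison; if the primary RT-PCR model adjusts for previous vaccination, as one section says and another does not, they are overstated once current and previous vaccination are moderately correlated

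*Protocol article*

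**What the plan says.** **Power.** The Sample size section builds each figure from a swab count, a vaccinated share, a positivity and a VE. For children, "we estimate a vaccination rate of 60% among children targeted for receipt of LAIV and a swab positivity rate of 20% among the unvaccinated", and then "This should give 90% power to detect a VE of 31% based on 1650 swabs in one season". For people aged 65+, with 70% vaccinated and 10% positivity, "we anticipate an 80% power to detect a VE of 39% where we estimate that there will be 1800 swabs each year". The only stated shortfall is clustering: "These powers above do not take into account design effects for the clustering of patients within GP practices". It is given as a design effect below 7%, worth about two percentage points of detectable VE.

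**Analysis.** In the RT-PCR outcomes section, VE is one minus an odds ratio, and "the OR is derived from the coefficient of vaccine status in the model". That section lists gender, age, deprivation, at-risk group and a spline for time as adjustments. Previous vaccination is not among them.

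Two other places include it. The section on patient characteristics and confounding factors has a previous-vaccination variable among the confounders. The Non-specific clinical outcomes section says: "In all models used to estimate the VE, we will adjust for variables associated with the receipt of a vaccination and effect modifiers, such as", and the examples that follow include vaccination in the previous influenza season.

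**The concern.** Adjusting for a covariate that predicts exposure leaves less independent variation in exposure, which widens the confidence interval of the vaccine coefficient. The plan itself describes these covariates as associated with receiving the vaccine. A power figure that ignores them describes a more precise analysis than the one to be reported.

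The 65+ and asthma groups carry the point, because they are targeted every season and last season's vaccination could predict this season's well. A non-significant adjusted VE in either group might be read as lack of effectiveness when the analysis did not have the power stated for it. Because the Sample size section names clustering as the one thing left out, a reader will take about two percentage points of VE as the whole gap.

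**Working it through.** **Inputs.** From Statistical analysis: "A 5% significance level will be used for hypothesis tests for the primary outcome" and "All p values will be two sided". From Sample size: N swabs, vaccinated share v, positivity p in the unvaccinated (for asthma, the overall figure of around 15% is used as p), and VE. The correlation ρ between current and previous vaccination is in neither section and is assumed.

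**Step 1: reproduce the plan's figures.** Let n₁ = N(1−v), n₂ = Nv and q = p(1−VE), with p̄ the average positivity over all N swabs. Then

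- s₀ = √[p̄(1−p̄)(1/n₁ + 1/n₂)]
- s₁ = √[p(1−p)/n₁ + q(1−q)/n₂]
- power = Φ[(p − q − 1.96 s₀)/s₁]

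For 65+ at 10%: n₁ = 540, n₂ = 1260, q = 0.10 × 0.61 = 0.061, p̄ = (54 + 76.86)/1800 = 0.0727, s₀ = 0.01335, s₁ = 0.01456. Power = Φ[(0.039 − 0.0262)/0.01456] = Φ(0.88) = 81.1%.

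| Scenario | N | v | p | VE | Stated | Recomputed |
|---|---|---|---|---|---|---|
| Children, one season | 1650 | 60% | 20% | 31% | 90% | 91.1% |
| Children, two seasons | 3300 | 60% | 20% | 22% | 90% | 90.1% |
| 65+ | 1800 | 70% | 10% | 39% | 80% | 81.1% |
| 65+ at peak | 1800 | 70% | 20% | 31% | 90% | 90.0% |
| Asthma, two seasons | 1260 | 40% | 15% | 35% | 80% | 78.7% |

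All five agree within 2 points. The figures are crude comparisons with no margin for adjustment.

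**Step 2: add previous vaccination.** With that covariate alone, R² = ρ², the variance inflation factor is 1/(1−ρ²), and the effective number of swabs is N(1−ρ²). For 65+ at 10% and ρ = 0.5, effective N = 1800 × 0.75 = 1350, s₀ = 0.01542 and s₁ = 0.01682. Power = Φ[(0.039 − 0.0302)/0.01682] = Φ(0.52) = 69.9%. VE stays on the risk-ratio scale that reproduces the plan's figures, so that only the effect of adjustment changes.

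| ρ (assumed) | Inflation | 65+ at 10% (stated 80%) | 65+ at 20% (stated 90%) | Asthma (stated 80%) |
|---|---|---|---|---|
| 0.2 | 1.04 | 79.6% | 88.9% | 77.0% |
| 0.3 | 1.10 | 77.6% | 87.3% | 74.7% |
| 0.5 | 1.33 | 69.9% | 80.6% | 66.1% |
| 0.7 | 1.96 | 54.6% | 65.0% | 49.4% |

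**Step 3: what ρ means.** If uptake is the same in both seasons and a share a of last season's vaccinees is revaccinated, then ρ = (a − v)/(1 − v). For 65+, ρ = 0.5 needs a = 0.70 + 0.5 × 0.30 = 85%. For asthma it needs 0.40 + 0.5 × 0.60 = 70%.

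**Step 4: detectable VE at the stated power.**

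| | 65+ at 10% | 65+ at 20% | Asthma |
|---|---|---|---|
| Unadjusted | 38.5% | 31.0% | 35.5% |
| Design effect 1.07 alone | 39.7% | 32.0% | 36.7% |
| ρ = 0.5 alone | 43.6% | 35.3% | 40.5% |
| ρ = 0.7 alone | 51.4% | 42.0% | 48.2% |

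The disclosed clustering effect equals an inflation of 1.07, that is ρ² = 1 − 1/1.07 = 0.065, or ρ of about 0.26. Above that value, the undisclosed effect is the larger.

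**Step 5: check by another route.** The expected information of a logistic model holding both current and previous vaccination, at ρ = 0.5, gives 69.9% (65+ at 10%), 81.0% (65+ at 20%) and 65.8% (asthma).

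**The case against.** Five objections deserve an answer.

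- **The primary model may not contain the variable.** The RT-PCR outcomes section does not list it. The sentence about all models stands under the non-specific outcomes heading, and its examples include the Charlson score, which the confounder section keeps for non-specific outcomes and adverse events. This stands. But the sentence says all models, and the confounder section lists previous vaccination without such a limit. The text supports both readings, so it has to be reconciled.
- **The correlation is unknown.** This stands too. A reader might infer that the adjusted VE lacks the stated power outright. The documents do not support that: they give no repeat-vaccination rate, and at ρ = 0.2 only asthma is more than 2 points below its stated power. The confounder section also speaks of previous seasons in general, whereas the working uses one earlier season.
- **The arithmetic is sound and unadjusted planning is common.** True, and no arithmetic error is alleged. The difficulty is that the section names clustering as what its powers leave out, while the plan elsewhere commits to a second source of lost precision.
- **Children.** A reader might extend the loss to all five figures. Live attenuated vaccine was introduced in 2013/2014, so few children would have had a vaccination the season before, and the loss there is probably small.
- **The data already exist and pooling is allowed.** Restating power changes no swab count, any imprecision will show in the confidence interval, and the Annual and pooled analyses section permits pooling for precision. That limits the consequence. Pooling is no further remedy for the asthma figure, however, since its 1260 swabs already cover two seasons.

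**Conclusion.** The point holds conditionally. It is established that the stated powers describe an unadjusted comparison, that they allow for clustering only, and that the sections disagree on whether the primary RT-PCR model adjusts for previous vaccination.

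If it does, the powers for 65+ and asthma are overstated once the correlation is moderate: by about 2 to 5 points at 0.3, 9 to 14 at 0.5 and 25 to 31 at 0.7, measured against the stated figures. These sizes rest on an assumed correlation, on adjustment for previous vaccination alone, and on VE held on the plan's own scale. If previous vaccination is not in the primary model, this loss does not arise there.

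The difference between one minus a risk ratio and one minus an odds ratio is a separate matter and is not counted here.

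**What to change.** 1. State whether the primary RT-PCR model includes previous vaccination, and make the RT-PCR outcomes, Non-specific clinical outcomes and confounder sections agree.
2. If it does, label the present powers in the Sample size section as unadjusted. Restate power and detectable VE with the expected swabs divided by 1/(1−R²), taking R² from a regression of current vaccination on the planned covariates in the SIVE or PIPER data. Apply the clustering effect on top.
3. For 65+ at 10% positivity, if a single season then falls short, name the multi-season estimate as the one expected to have adequate power.
4. For asthma, where two seasons are already pooled, restate the detectable VE.

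The cost is one regression in data the plan already draws on and a reworded paragraph, with no extra patients or swabs. The downside is that the stated detectable VEs become less favourable.
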